### Data collection and quality management

Several quality assurance practices should be established and undertaken both before and during project implementation. The design of the project (Fig. 1) was based on previous studies undertaken by both the Department of Infectious Disease and the Department of Neurology of the Huashan Hospital affiliated with Fudan University. All relevant personnel involved in the project, including clinicians, laboratory, and project management personnel have received uniform training; which includes theoretical explanations and internship operations. Furthermore, we have devised a number of inclusion standards and involved clinicians have undergone specialized training on relevant topics and become familiar with the principles and standards of case inclusion. To ensure that cases are representative, every case that meets the inclusion criteria during the implementation of the project must be included and cannot be selected or omitted. Each case will be reviewed by the subject person in charge of Huashan Hospital affiliated with Fudan University.

Data collection also requires quality management of all aspects. Clinicians responsible for filling in the subject information forms have received uniform training on the subject. They will have a clear understanding of the questions in the information sheet before formally asking the participants and will be able to fill in the relevant content accurately according to the requirements in the uniformly designed case report form (CRF). The clinician must ask the participants the questions face to face while completing the form, rather than making assumptions or filling it out by recollection afterwards.

To ensure the authenticity and objectivity of the subject material, all relevant forms should be properly stored. All registration books and form cards must be kept in a suitable place that is safe from flooding, burning, tearing, smearing, and so on. A person should be dedicated to ensure that all information can be accessed after the on-site investigation.

In order to ensure that each center conducts the research in strict accordance with the design plan, and that the data is true and credible, the project leader will be supervised by the Encephalitis/Meningitis Research Group of Huashan Hospital affiliated with Fudan University, once every 2 months. Supervisors will be assigned by the Huashan Hospital affiliated with Fudan University.

### Adverse event management

Potential adverse events and their management have been evaluated. In this study, an additional 13 ml of peripheral blood and 8 ml of CSF will be drawn during routine clinical examinations in the enrolled participants No additional operations or costs are required. However, the process to collect extra blood and CSF, medical history and other information may cause psychological discomfort to the participants. There might also be risks, such as short-term pain and local bruising during blood withdrawal and lumbar puncture. Some people may experience mild dizziness, and in extremely rare occasions, an infection at the needle site may occur. Collection of extra CSF during lumbar puncture may potentially cause mild headaches and backaches following this process.

To further evaluate and avoid adverse events, we will record these events and they will be attended to by physicians. If a patient has any psychological discomfort during the collection of their medical history, the researcher will provide timely comfort and notify the designated personnel of the research group to record and evaluate this event within 2 h. If verbal comfort is ineffective for any participant, such as in the cases of depression or mania and so on, a psychologist will be required to conduct an evaluation and psychological counseling within 12 h, and this will be recorded by the designated personnel from the research team. Fluid infusion may be administered to participants with mild headaches and backaches after lumbar puncture. In the event of unexpected injury or loss related to this study, the patient will receive appropriate treatment or compensation. All adverse events in this clinical study will be recorded in detail by a dedicated person. Any serious adverse events will be handled and recorded by a dedicated person and reported to the ethics committee and relevant departments timely.

### Assessment and analysis of outcomes

The primary and secondary outcomes between Group I and Group II will be compared. Primary outcomes are the initial time of targeted treatment and mRS score on the 30th day whilst secondary outcomes include CSF index remission rate on the 14th day, mortality rate on the 30th day, and the evaluation of diagnostic efficacy. Through these assessments, we may explore the best diagnostic algorithm for encephalitis/meningitis, and finally determine its optimal treatment.

The results for the trial outcomes will be analyzed through the following methods. First, we will review whether the enrolled cases meet the selection and exclusion criteria, and whether the actual number of enrolled, excluded and dropped cases in each center are accounted for at the end of the study; we will then perform a comparability analysis. Data relating to demographic characteristics, general and baseline (before the test) conditions will be compared between the two groups. The statistical analyses to be employed include two-sided t-tests, Wilcoxon tests, and chi-square tests—which will compare the outcomes between the two groups. A P value ≤ 0.05 was considered statistically significant. Excel was adopted for the management of data and the performance of statistical analysis after verification. SPSS 11.0 and PRISM 9.0 were the software used for statistical analyses.

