**Methods:**

IMPROVE is a multicenter, open label, randomized controlled clinical trial that aims to evaluate the diagnostic performance, applications, and impact on patient outcomes of a new diagnostic algorithm that combines metagenomic next-generation sequencing (mNGS), multiplex polymerase chain reaction (PCR) and autoimmune antibody testing. The enrolled patients will be grouped into two parallel groups, multiplex PCR test plus autoimmune antibody group (Group I) or the mNGS plus autoimmune antibody group (Group II) with a patient ratio of 1:1. Both groups will be followed up for 12 months. The primary outcomes include the initial time of targeted treatment and the modified Rankin scale score on the 30th day of the trial. The secondary outcomes are the cerebrospinal fluid index remission rate on the 14th day, mortality rate on the 30th day, and an evaluation of diagnostic efficacy. The two groups are predicted to comprise of 484 people in total.

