### Study flowchart and clinical evaluation of enrolled patients

Adult patients who meet the inclusion criteria will be eligible (Table 1). Eligible patients with suspected encephalitis/meningitis will be included after signing the informed consent forms. As outlined above, the participants will be randomly assigned in a 1:1 ratio to Group I or Group II. The randomization is performed through the online central randomization system stratified by the study sites (Clinflash, China). To facilitate autoimmune encephalitis antibody tests and molecular etiological examinations, 13 ml of peripheral blood and 8 ml of cerebrospinal fluid (CSF) will be collected. The first screen will include basic patient characteristic, as well as additional information such as present history, functional assessments (modified Rankin Scale [mRS], Glasgow outcome score [GOS] and EuroQol-5 Dimension (EQ-5D)), physical examinations, cranial magnetic resonance imaging (MRI), blood examinations including routine blood tests, C-reactive protein, synchronous glucose, D-dimer, *Treponema pallidum* particle agglutination assay/rapid plasma reagin, thyroid hormones and thyroid-related antibodies; CSF pressure, biochemical and routine tests; and etiological examinations of CSF including latex agglutination test, ink stain, and bacterial, fungi and tuberculosis cultures. Electroencephalograms are to be performed according to clinical necessity.

**Table 1 Tab1:** Inclusion and exclusion criteria

Inclusion criteria
• Aged from 18 to 80 years old
• Without clear diagnosis
• Without effective antimicrobial therapy
• The suspected meningitis/encephalitis patients should meet the ① or ② items as following:
① Suspected meningitis: Rapid onset fever (> 38.5 °C). with at least one of the three manifestations as following:
(1) Neck stiffness
(2) Alteration of consciousness
(3) Other signs indicating meningitis, for example, meningeal irritation sign
② Suspected encephalitis: Altered consciousness because of unidentified reasons that persisted for longer than 24 h, including lethargy, irritability, or a change in personality, and have at least one of these manifestations:
(1) Fever or history of fever (≥ 38 °C, oral temperature) during the presenting illness
(2) Seizures not explained by a previously known seizure disorder
(3) CSF pleocytosis (white blood cell count of more than 4 cells per μl)
(4) Electroencephalographic (EEG) findings indicative of encephalitis

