### Sample size calculation

The predicted sample size was calculated using the PASS 11 software. Assuming hazard ratio (HR) = 1.48 and θ = 1, and according to previous research, pE = 0.7, PA = 0.5, each group requires 230 samples. Assuming a 5% drop-out rate in follow-up, each group needs 230 × 1.05 = 242 people; therefore, the total sample size of the two groups combined is calculated to be 484 people.

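### The trial is sized on a hazard ratio, but the tests named for the outcomes include no time-to-event method for the primary outcome, time to targeted treatment

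*Protocol article*

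**What the plan says.** Under Assessment and analysis of outcomes, the protocol article states: "Primary outcomes are the initial time of targeted treatment and mRS score on the 30th day". The Abstract agrees.

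The Sample size calculation section works on a hazard-ratio scale: "Assuming hazard ratio (HR) = 1.48 and θ = 1, and according to previous research, pE = 0.7, PA = 0.5". It arrives at 230 per group, raised to 242 for drop-out. It does not define the symbols, name the endpoint behind the hazard ratio or state the power.

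For the comparison of outcomes the article says: "The statistical analyses to be employed include two-sided t-tests, Wilcoxon tests, and chi-square tests". The sentence goes on to apply these tests to the outcomes of the two groups and does not assign a test to each outcome. No log-rank, Kaplan-Meier or Cox method appears anywhere in the article. Nor does a censoring rule, or a value for patients who never receive targeted treatment.

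The article itself shows that such patients will occur. The eligibility and classification text has a residual category of unknown origin. The Abstract puts unknown origin at 30–40% of patients in general, and the Background gives mortality of up to 5–10%.

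**The concern.** The effect measure used for sizing and the tests listed for analysis do not belong together. A hazard ratio describes the rate of reaching targeted treatment over time among everyone still at risk. A t-test or Wilcoxon test compares observed times. A chi-square test compares proportions and ignores time.

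The difficulty lies with patients who have no time to record. If a t-test or Wilcoxon test is run on the recorded times, these patients drop out and the comparison is between the treated in one arm and the treated in the other. Whether a patient is treated is decided after randomisation and depends on the diagnostic strategy under study, so the two treated subsets need not be comparable.

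Two things would be at stake. Much of a real benefit may lie in more patients being treated by a given day, and a treated-only comparison cannot see that. Also, if one strategy adds diagnoses that arrive later, its mean time among the treated gets longer although more of its patients are treated.

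**Working it through.** **1. Does the stated 230 come from a hazard-ratio calculation?**

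Inputs from Sample size calculation: HR 1.48, and the values 0.7 and 0.5. Allocation is 1:1 (Study flowchart section). Two-sided 0.05 follows Assessment and analysis of outcomes. Assumptions: 90% power, a test against HR = 1, and 0.7 and 0.5 read as the event probabilities of the two arms (mean 0.6).

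Schoenfeld: events = (z₀.₉₇₅ + z_power)² / (0.25 × (ln HR)²).

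- 90% power: (1.960 + 1.282)² / (0.25 × 0.392²) = 273.5 events. Then 273.5 / 0.6 / 2 = 228 per group, against 230 stated.
- Freedman's formula, same inputs: 281 events, 235 per group.
- 80% power: 171 per group.
- 0.7 read as the overall event probability and 0.5 as the allocation share: 146, 196 and 242 per group at 80%, 90% and 95% power.
- Two-proportion test of 0.7 against 0.5: 93 per group at 80% power and 124 at 90%.

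A hazard-ratio calculation therefore comes close to 230 at an ordinary power, and a comparison of proportions does not. The reading is not unique: an event probability of 0.5 at 85% power gives 234. Nor is it fully coherent, since proportional hazards with event probabilities 0.7 and 0.5 would imply HR = ln 0.3 / ln 0.5 = 1.74, not 1.48.

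**2. Would the stated size suit a log-rank or Cox analysis?**

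Power = Φ(√events × ln HR / 2 − 1.96).

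- Mean event probability 0.6: 460 × 0.6 = 276 events, power 90.3%.
- Overall event probability 0.7: 460 × 0.7 = 322 events, power 94.0%.

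So the analysis can change without changing the sample size.

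**3. Illustration under proportional hazards**

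Assumptions: 230 per arm, exponential times, follow-up cut at day 30, HR 1.48, 70% treated overall. Solving 1 − (1 − p)^1.48 with a mean of 0.70 gives 63% treated in Group I and 77% in Group II. Simulated power at two-sided 0.05:

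| Analysis | Power |
|---|---|
| Log-rank, all patients | about 94% |
| t-test, treated only | about 22% |
| Wilcoxon, treated only | about 22% |
| Wilcoxon, untreated ranked last | roughly 90–93% |
| Chi-square, ever treated by day 30 | roughly 90–93% |

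With 50% of Group I treated by day 30 instead, log-rank power is 89% and the treated-only tests have about 12%.

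**4. Illustration with later extra diagnoses**

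Assumptions, none from the article: 62.5% of each arm treated at a mean of 4 days, plus 15 percentage points more in Group II treated at a mean of 8 days. The mean among the treated in Group II is then about (62.5 × 4 + 15 × 8) / 77.5 = 4.8 days, against 4 in Group I, although more of Group II is treated.

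How often a treated-only test declares Group I significantly faster depends on the spread of the times. From exponential times to less dispersed gamma times (shape 4), the range is roughly 20–80% for the t-test and 15–50% for the Wilcoxon test. Over the same range the log-rank test favours Group II in about 73–84% of trials. These figures show the direction of the problem and do not predict its rate in this trial.

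**The case against.** The strongest reply is that the article never says it will analyse treated patients only. The test list serves all outcomes: a Wilcoxon test suits the day-30 mRS, and a chi-square test suits remission and mortality rates. The list is introduced with a non-exhaustive verb, and a separate analysis plan, not shown here, may name a survival method. Censoring details are normally left to such a plan.

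Much of this stands. A reader might infer that the listed tests cannot handle never-treated patients at all. That is too strong: with complete follow-up, a Wilcoxon test that ranks them last, or a chi-square test on treatment by a fixed day, includes everyone and in the first illustration loses little power. A reader might also infer that 0.7 in the sizing means 30% are never treated, or that the 30–40% of unknown origin are the never-treated. The article supports neither. The symbol is undefined, the 30–40% is a background figure, and patients of unknown origin go on to further tests that may lead to targeted treatment.

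What does not stand is that this is mere missing detail. The article states the hazard ratio and states the tests that will compare the outcomes, and the two do not match. It gives no worst-rank or fixed-day rule. The sizing section does not name its endpoint, but time to targeted treatment is the only time-to-event primary outcome, and 0.5 to 0.7 does not fit mortality of 5–10%.

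**Conclusion.** The mismatch is real. The trial is sized on a hazard ratio, and the tests named for the outcomes neither estimate nor test one, nor handle censoring, although some patients will have no treatment time.

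The harm is conditional. It arises if a t-test or Wilcoxon test is applied to recorded times, which the article neither states nor rules out. In that case power in the proportional-hazards illustration falls from about 94% to about 22%, given an assumed 70% treated by an assumed day 30. The comparison can also point the wrong way if the extra treated patients in Group II are treated later, at a rate too dependent on the assumed time distribution to quote as one figure.

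That the 230 was built for a survival analysis is a well-supported inference. It rests on an assumed 90% power and on reading 0.7 and 0.5 as arm event probabilities.

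**What to change.** In Assessment and analysis of outcomes, give this primary outcome its own analysis:

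- **Outcome and population:** time from randomisation to first targeted treatment, in all randomised patients by assigned group.
- **Test and estimate:** log-rank test stratified by site, matching the site-stratified randomisation, with a Cox hazard ratio and 95% confidence interval.
- **Untreated patients:** censored at a fixed day that the sponsor states in advance. Day 30 above is only an assumption of the illustration.
- **Death before targeted treatment:** handled as a competing event, with cumulative incidence curves by group.
- **Other outcomes:** keep the t, Wilcoxon and chi-square tests for these.

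In Sample size calculation, name the endpoint behind the hazard ratio, define the symbols and state the power.

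The cost is wording. The sample size and the data collected do not change. In an open-label trial the change should be made before outcome data are compared by group.

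### The day-30 mRS comparison is unadjusted although randomisation is stratified by site and baseline mRS is recorded, so available precision is given up

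*Protocol article*

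**What the plan says.** Under Assessment and analysis of outcomes, the article names the outcomes: "Primary outcomes are the initial time of targeted treatment and mRS score on the 30th day". It lists the methods as "two-sided t-tests, Wilcoxon tests, and chi-square tests—which will compare the outcomes between the two groups", with the criterion "A P value ≤ 0.05 was considered statistically significant". Baseline data appear in that section only as a comparability check, in which "baseline (before the test) conditions will be compared between the two groups". No regression model, covariate or stratified test is named there or elsewhere in the article.

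Under Study flowchart and clinical evaluation of enrolled patients, the article says: "The randomization is performed through the online central randomization system stratified by the study sites". The same section lists, among the first-screen assessments, "functional assessments (modified Rankin Scale [mRS], Glasgow outcome score [GOS] and EuroQol-5 Dimension (EQ-5D".

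**The concern.** Two pieces of information that could sharpen the mRS comparison are in hand and go unused.

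- **Site.** Stratified randomisation balances the arms within sites, so differences between sites largely cancel out of the treatment contrast. A two-sample test that ignores site still counts those differences as noise. Its standard error is then too large whenever sites differ in outcome.
- **Baseline mRS.** This is the same scale as the outcome, measured before the tests are applied. Where it predicts day-30 mRS, adjusting for it removes variance that the unadjusted test leaves in.

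At stake is power and confidence-interval width for the patient-outcome primary endpoint. Interval width matters all the more because Study design describes the trial as one of non-inferiority.

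**Working it through.** **1. The plan's own sample size.** The article states "Assuming hazard ratio (HR) = 1.48 and θ = 1, and according to previous research, pE = 0.7, PA = 0.5, each group requires 230 samples", then "Assuming a 5% drop-out rate in follow-up, each group needs 230 × 1.05 = 242 people". Power is not stated, so 90% with two-sided 0.05 is assumed here.

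- Events (Schoenfeld) = 4(1.960 + 1.282)² / (ln 1.48)² = 274.
- Mean event probability = (0.7 + 0.5)/2 = 0.6.
- Per arm = 274 / 0.6 / 2 = 228.3, so 229, against 230 stated.
- 230 × 1.05 = 241.5, so 242 per arm and 484 in total, as stated.

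The match is not unique. For example, Freedman's formula at 90% gives 234.2 per arm. What matters here is that the calculation rests on a hazard ratio. It sets no effect or power for mRS, so it neither supports nor contradicts this point.

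**2. Adjustment for baseline mRS (linear-model illustration).** Inputs are 230 per arm (Sample size calculation), two-sided 0.05, and a correlation r between baseline and day-30 mRS. The documents give no r, so a range is assumed.

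- Variance factor = 1 − r². The n per arm with the same precision as 230 unadjusted = 230(1 − r²), rounded up.
- Adjusted power = Φ(k/√(1 − r²) − 1.960). For an effect with 80% unadjusted power, k = 1.960 + 0.842 = 2.802. For one with 90%, k = 1.960 + 1.282 = 3.242.
- Example, r = 0.3: 2.802/√0.91 = 2.937; 2.937 − 1.960 = 0.977; Φ(0.977) = 0.836.

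| r (assumed) | Variance cut | Same-precision n per arm | Power, if 80% unadjusted | Power, if 90% unadjusted |
|---|---|---|---|---|
| 0.3 | 9% | 210 | 83.6% | 92.5% |
| 0.4 | 16% | 194 | 86.4% | 94.3% |
| 0.5 | 25% | 173 | 89.9% | 96.3% |
| 0.6 | 36% | 148 | 93.8% | 98.2% |

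**3. Simulation check.** A seven-level mRS was simulated for 460 patients with site-stratified 1:1 allocation and 3,000 replicates. The 20 sites, the site intraclass correlation (ICC) of 0 to 0.10 and the treatment shift of 0.27 latent SD are all assumed. The adjusted analysis was a linear model with site and baseline mRS.

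| Quantity | Result |
|---|---|
| Power, unadjusted t or Wilcoxon | 79% to 81% |
| Power, adjusted, r = 0.3 | 82.5% to 86.4% |
| Power, adjusted, r = 0.5 | 87.5% to 90.7% |
| Type I error, unadjusted, ICC 0 | 4.8% to 5.0% |
| Type I error, unadjusted, ICC 0.10 | 4.1% to 4.5% |

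The Monte Carlo standard error of a 5% rate is √(0.05 × 0.95/3000) = 0.4 percentage points. The unadjusted tests are therefore valid, and the ICC 0.10 results fit the mild conservatism expected when sites differ.

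**The case against.** The strongest reply is that this is a condensed article. Its list of methods is introduced as inclusive rather than exhaustive, and covariates are often left to an analysis plan, which is not shown here. An unadjusted Wilcoxon test is also a legitimate primary analysis. Part of this stands: an unseen plan could add an adjusted model. But the article does state its methods, those methods ignore the design's own stratifier and the baseline value of a primary outcome, and nothing in the text points to any other analysis.

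The reply on size stands in full. The article gives no correlation, no between-site variance and no number of sites. The encephalitis entry route requires altered consciousness, which may narrow the spread of baseline mRS and put the gain at the low end. The limitations in the Discussion concede that some hospitals lack treatment and testing capability, but the only consequence named is unidentified pathogens, not different mRS. The factor 1 − r² belongs to a linear model and does not carry over to the standard error of a proportional-odds coefficient.

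Three stronger readings might be inferred, and the documents do not support them:

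- **The test is invalid, or chance imbalance biases it.** The simulated type I error is at or slightly below 5%. Chance imbalance in a randomised comparison costs precision; it does not introduce bias.
- **Three tests compete for mRS, allowing a choice after results are seen.** The sentence covers all outcomes together, and its ordinary reading is one test per type of data. Matching tests to outcomes is commonly left to the analysis plan.
- **The mRS endpoint is underpowered.** No mRS effect or power target is stated, so no shortfall can be shown.

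**Conclusion.** The point holds as a moderate one about efficiency. The stated analysis of day-30 mRS leaves out the randomisation stratum and a recorded baseline value of the same scale. It gives up precision and is slightly conservative if sites differ in outcome.

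The gain from adjustment at 230 per arm runs from about 4 points of power (80% to 84%, r = 0.3) to about 14 (80% to 94%, r = 0.6). From 90% unadjusted power it runs from 2.5 to about 8 points. These figures rest on assumed correlations and a linear model. Site adjustment adds to them only to the extent that sites differ in outcome, which the documents do not quantify.

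**What to change.** In Assessment and analysis of outcomes, state that:

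- the primary analysis of day-30 mRS adjusts for baseline mRS and study site, for example by ordinal regression or ANCOVA, with small sites pooled by a rule fixed in advance or a random site effect;
- it reports an effect estimate with a 95% confidence interval;
- the other between-group outcome comparisons are stratified by site.

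A van Elteren test (site-stratified Wilcoxon) would deal with site but not with baseline mRS.

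Site and first-screen mRS are already recorded, so the change needs no new data. It costs slightly more analysis work. With an ordinal model, the odds ratio becomes conditional on baseline mRS and site rather than marginal, and the report should say so.

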## Methods

### Study design

This study is a multicenter open label, randomized controlled clinical trial of non-inferiority with two arms recruiting patients with suspected encephalitis/meningitis. The enrolled patients will be grouped into two parallel groups with a ratio of 1:1, those whose diagnoses were achieved through multiplex PCR tests plus autoimmune antibody analyses (Group I), and those being assessed through the use of mNGS plus autoimmune antibody testing (Group II). The detailed study schematic is shown in Fig. 1.

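### Two primary outcomes share one unsplit P ≤ 0.05 threshold with no joint success rule; if either one suffices, the two-sided family-wise error is up to 9.75%

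*Protocol article*

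**What the plan says.** Protocol article, *Assessment and analysis of outcomes*: "Primary outcomes are the initial time of targeted treatment and mRS score on the 30th day". The Abstract (*Methods*) names the same pair: "The primary outcomes include the initial time of targeted treatment and the modified Rankin scale score on the 30th day of the trial".

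The same outcomes section describes the comparisons as follows: "The statistical analyses to be employed include two-sided t-tests, Wilcoxon tests, and chi-square tests". It then gives the only decision threshold in the article: "A P value ≤ 0.05 was considered statistically significant". No section adds a rule for combining the two primaries.

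*Study design* calls this a "randomized controlled clinical trial of non-inferiority with two arms", with patients "grouped into two parallel groups with a ratio of 1:1". The article gives no margin.

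*Sample size calculation* reads "Assuming hazard ratio (HR) = 1.48 and θ = 1" and then "pE = 0.7, PA = 0.5, each group requires 230 samples". It names no outcome, alpha or power, and has no separate calculation for mRS.

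**The concern.** Two primaries with one undivided threshold leave the trial's conclusion open. The outcomes answer different questions: one measures how soon the diagnostic strategy leads to treatment, the other how disabled the patient is at day 30. They could well diverge, for example if treatment starts earlier but mRS does not change. The article gives no agreed reading of such a split result. A sponsor applying the text exactly could report either outcome as a significant primary result at the full 5%.

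If that is how success is judged, the trial has two chances at a 5% error and the overall error exceeds 5%. The non-inferiority label adds to the ambiguity. The listed tests are ordinary difference tests, so the article does not settle what a positive result on either primary would mean.

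**Working it through.** **The plan's own figures.** The dropout step reproduces: 230 × 1.05 = 241.5, rounded up to 242, and 242 × 2 = 484. The 230 itself cannot be confirmed, because no alpha or power is stated. Reading HR = 1.48 as the alternative, pE = 0.7 as the overall event probability and PA = 0.5 as equal allocation (all assumptions), Schoenfeld's formula gives

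events = 4 (z_α + z_power)² / (ln 1.48)², and n per group = events / (2 × 0.7).

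- Two-sided 0.05: 147, 196 and 243 per group at 80%, 90% and 95% power. None is 230.
- Two-sided 0.025 with 90% power: 230.7 per group.
- One-sided 0.05 with 80% power: 229.9, but as a total, not per group.

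Two different unstated settings land on 230, so the planning alpha cannot be recovered. In particular, the match at 0.025 does not show that an alpha split was planned.

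**Family-wise error.** Inputs: two primaries and a threshold of 0.05, both from *Assessment and analysis of outcomes*. The tests are taken as two-sided; the article attaches that word to the t-tests, and here it is assumed for both primaries. Both null hypotheses are taken as true. The correlation r between the test statistics is not in the documents, so a range is shown.

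- Independent tests: 1 − (1 − 0.05)² = 1 − 0.9025 = 0.0975.
- Correlated tests: 1 − P(|Z₁| < 1.96 and |Z₂| < 1.96), with (Z₁, Z₂) standard bivariate normal.
- Both significant: 0.05 + 0.05 − P(at least one).

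| r | At least one significant | Both significant |
|---|---|---|
| 0 | 9.75% | 0.25% |
| 0.3 | 9.51% | 0.49% |
| 0.5 | 9.07% | 0.93% |
| 0.8 | 7.81% | 2.19% |
| 0.9 | 7.04% | 2.96% |

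The last column is for two true nulls. If only one null is true, a both-required rule still has error of at most 5%, because the true null must itself be rejected at 0.05.

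**Direction.** These figures count rejections either way. For false findings in one given direction, the independent case is 1 − 0.975² = 4.94% against 2.5%. The ratio is nearly the same.

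**After a 0.025/0.025 split.** Independent: 1 − 0.975² = 4.94%. Under any correlation: at most 0.025 + 0.025 = 5%.

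**Illustrative cost of a split.** Assume 460 × 0.7 = 322 events and a log-rank analysis. Then ln 1.48 × √322 / 2 = 0.392 × 17.94 / 2 = 3.52.

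- At two-sided 0.05: Φ(3.52 − 1.96) = 94.0%.
- At two-sided 0.025: Φ(3.52 − 2.24) = 89.9%.

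The loss is about 4 percentage points for HR 1.48.

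**The case against.** The strongest reply is that this is a condensed article. A success rule or multiplicity procedure commonly sits in the full protocol or SAP, neither of which is shown, and the threshold sentence may be no more than a general reporting convention. That has force against any claim that the trial has no rule at all. It does not remove the point, because the article does more than stay silent: it fixes one undivided threshold for the outcome comparisons and exempts neither primary. If a different rule exists elsewhere, the published sentence should agree with it.

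Other parts of the reply stand and limit the point:

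- A reader might infer that the trial's error rate is in fact nearly doubled. The article does not say that one significant primary makes the trial positive, and if both are required there is no inflation.
- A reader might infer that only time to targeted treatment sizes the trial. A hazard ratio suggests that outcome, but the sample size section names none.
- A reader might take 94% as the trial's power. It depends on assumed readings of pE and PA and on a log-rank analysis, which is not among the tests the article lists.
- Both outcomes are prespecified, so the freedom lies in which one decides the trial, not in what is measured.
- Under a non-inferiority label without a margin, a false positive is not fully defined. The figures above apply to difference hypotheses, which is what the listed tests address.

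**Conclusion.** The point holds conditionally. Two primaries, one unsplit 0.05 threshold and no success rule are facts of the article. If either primary alone can make the trial positive, the two-sided family-wise error is up to 9.75%, and still 7.8% at correlation 0.8, against 5%. If both must succeed, the error does not exceed 5% and the cost falls on power instead. The article does not say which applies, so it supports the statement that the error can nearly double, not that it does.

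The size rests on two-sided difference tests, both nulls true and an unknown correlation. It does not depend on any reading of the sample size inputs; only the illustrative cost of a split does. This should be settled before the data are analysed.

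**What to change.** In *Assessment and analysis of outcomes*, replace the single threshold, for the two primaries, with one stated rule that holds the overall error at 5%. Any of these would do:

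- **Holm or a 0.025/0.025 split.** Either outcome can then be claimed on its own. Under the illustrative assumptions above, a split lowers power for HR 1.48 from about 94% to about 90%. Holm gives at least the power of the split.
- **Fixed sequence.** Test time to targeted treatment first at 0.05 (the hazard ratio in the sample size section appears to refer to it), then day-30 mRS at 0.05 only if the first succeeds. The first test loses no power, but mRS cannot be claimed as confirmatory if that test fails.
- **Both required, each at 0.05.** No alpha is divided, but the power of the joint claim cannot exceed that of the weaker outcome, and the article gives no power basis for mRS.

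The choice depends on which claim the sponsor wants the trial to support. The same text should say which hypothesis each primary tests, superiority or non-inferiority, so that it agrees with *Study design*. If the full protocol or SAP already holds a rule, it is enough to bring the public text into line with it.

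The change is to analysis wording only and adds no patients. The power figures are illustrative, because the article states no alpha or power.
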